#### Patient selection

Patients will be recruited from the waiting list of the senior surgeon (PM) at the Orthopedic Department of the University Hospital of Patras, Greece. Patients with unilateral hip osteoarthritis for which THA is indicated will be randomized in two different groups. The preoperative raw data will include full demographic profile, patient age, sex, body mass index (BMI), the Charlson Comorbidity Index [49] and a standardized radiological work-up. Eligible patients for short-stem implantation will be between 50 and 80 years old and suffer from (1) primary osteoarthritis, (2) inflammatory arthritis, (3) avascular necrosis and (4) post-traumatic arthritis. Exclusion criteria will include any severe comorbidities affecting functional outcome (i.e., symptomatic lumbar pathology) as well as patients with poor bone stock and any femoral deformity precluding fit and fill in the metaphysis, such in cases of hip dysplasia and severe valgus or metaphyseal deformity secondary to fracture. Participants are free to withdraw from the study at any point or a participant can be withdrawn by the investigator. If withdrawal occurs, it will be documented on a participant “Change of Status” Form. In the event of withdrawal, patients will be invited to provide final primary endpoint data.

#### Randomization procedures

We used stratified block randomization consisting of a random sequence of blocks of 10 consecutive surgical procedures each. Randomization was performed in the operating theater, after anesthetic induction and just before incision, using a sequentially numbered opaque sealed envelope.

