#### Design

This study uses a prospective, randomized, parallel-group design with blinded treatment and assessment to compare the overall performance of two different short femoral stems, which are theoretically classified in the same main category. This paper is written according to the Standard Protocol Items: Recommendations for Interventional Trials (SPIRIT) 2013 Statement for reporting of clinical trial protocols (Fig. 5, Additional file 1).

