#### Intervention

All patients will receive the type of implant to which they have been randomly allocated and thus two groups of patients will be created: group A: Tri-Lock BPS group and group B: Minima S Monolithic Femoral Stem implantation group.

The same senior surgeon (PM) will perform all the arthroplasties with a standardized operative technique through a mini-posterior approach. The femur will be prepared in a broach-only fashion and then the prosthesis will be impacted until a tight metaphyseal fit is achieved. The acetabulum will be prepared in a standardized fashion according to the manufacturer’s manual with the intention of using larger femoral heads (28–32 mm). Ceramic or polyethylene inserts and ceramic or metallic heads in respect will be used according to surgeon’s preference and patients age. All patients in both groups will undergo the same postoperative physiotherapy protocol, which consists of gradual progression from up-to-chair tolerance to ambulation and stair-climbing under the supervision of a certified physical therapist. Patients who manage to complete inpatient physical therapy for independent full weight-bearing would be discharged from further therapy but those with less compliance will continue further rehabilitation.

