#### Analysis

##### Power and sample size calculation

The minimal clinically important differences (MCID) for sample calculation have been defined according to the literature at 25 points for the WOMAC score, 20 points for the HHS and 12% difference for the SF-36 score. In order to achieve a 80% power or better the effect size is expected to lie between 0.25 and 0.6, suggesting a sample size of 45 patients in each group [61].

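### A single fixed block length of 10, with one surgeon who supplies the patients and implants every stem, lets some late-block allocations be inferred when patients are judged eligible or scheduled

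*Protocol article*

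**What the plan says.** The Randomization procedures section gives one block length and no other: "We used stratified block randomization consisting of a random sequence of blocks of 10 consecutive surgical procedures each". It then describes concealment: "Randomization was performed in the operating theater, after anesthetic induction and just before incision, using a sequentially numbered opaque sealed envelope".

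Two other sections determine who can see what:

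- Patient selection: "Patients will be recruited from the waiting list of the senior surgeon". Its exclusions include "patients with poor bone stock and any femoral deformity precluding fit and fill in the metaphysis". Examples of deformity follow, but no measurement cut-off.
- Intervention: the same senior surgeon "will perform all the arthroplasties with a standardized operative technique through a mini-posterior approach".

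The Design section says: "This study uses a prospective, randomized, parallel-group design with blinded treatment and assessment". It does not say who is blinded. The sample size section plans 45 patients per group.

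**The concern.** A surgeon who implants a straight wedge stem in one patient and a shorter curved stem in the next knows which was used. That the surgeon is unmasked is an inference, but a safe one, and the blinding described under Design cannot extend to this person. The patients also come from this surgeon's list, so it is reasonable to infer that the surgeon influences who is judged suitable and in what order they are operated on. The article does not say who screens or schedules.

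If block length is fixed and known, past allocations reveal how many places each arm has left. Late in a block the next stem becomes likely, and sometimes certain. A borderline femur could then be accepted, declined or moved according to the stem expected, without any intent to do so.

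The first primary endpoint counts fracture, loosening and revision among the hip-related complications. A surgeon's view of bone stock and fit could plausibly bear on these. With 45 per arm, moving a few difficult femurs could affect that comparison. The Limitations section treats the single surgeon only as a matter of generalisability.

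**Working it through.** The article gives no figure for predictability, so there is none to reproduce.

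**Inputs**
- Block length 10 (Randomization procedures).
- 45 per group, so 90 patients and 90 / 10 = 9 blocks (Power and sample size calculation).
- Assumed, not stated: 5:5 balance in each block, one series, and a surgeon who knows the block length.

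**Step 1. Allocations known with certainty, all earlier patients in the block operated on.** There are C(10,5) = 252 balanced sequences. Position k is certain when one arm has used its five places in the first k − 1 positions, with probability 2 × C(k − 1, 5) / 252:

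| Position | Calculation | Probability |
|---|---|---|
| 6 | 2 × 1 / 252 | 0.008 |
| 7 | 2 × 6 / 252 | 0.048 |
| 8 | 2 × 21 / 252 | 0.167 |
| 9 | 2 × 56 / 252 | 0.444 |
| 10 | 2 × 126 / 252 | 1.000 |

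The sum is 420 / 252 = 1.67 per block, or 1.67 × 9 = 15 of 90.

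**Step 2. Best guess.** With a and b places left, guessing the arm with more places is right with probability max(a, b) / (a + b). Averaged over the 252 sequences, the chance of a correct guess with j = 0, 1, …, 9 allocations known is 0.500, 0.556, 0.556, 0.595, 0.595, 0.643, 0.643, 0.722, 0.722 and 1.000. The sum is 6.53 of 10, or 65.3%. Over nine blocks that is about 59 of 90, against 45 by chance.

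**Step 3. Allow for booking ahead.** Eligibility and scheduling are decided before surgery. If L trial patients are already booked but not yet operated on, the L most recent allocations are unknown when the decision is made. The last L terms of each sum then drop out; for guessing, each is replaced by 0.5.

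| L | Certain per block | Certain of 90 | Correct guesses per block |
|---|---|---|---|
| 0 | 1.67 | 15 | 6.53 (65%) |
| 1 | 0.667 | 6 | 6.53 − 1.000 + 0.5 = 6.03 (60%) |
| 2 | 0.222 | 2 | 6.03 − 0.722 + 0.5 = 5.81 (58%) |
| 3 | 0.056 | 0.5 | 5.81 − 0.722 + 0.5 = 5.59 (56%) |
| 5 | 0 | 0 | 5.59 − 2 × 0.643 + 2 × 0.5 = 5.30 (53%) |

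The article does not give L.

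**Step 4. Would a shorter fixed block help?** No. If the length is known, the certain share is 20.0% for blocks of 8, 25.0% for 6 and 33.3% for 4, against 16.7% for 10. Correct guesses rise to 66.6%, 68.3% and 70.8%. The weakness is a fixed, knowable length, not the choice of 10.

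**The case against.** The strongest reply is that the scheme already has real protection. Sequentially numbered opaque envelopes opened after induction keep the current allocation hidden during selection, and 10 is long for a fixed block. Nothing says the surgeon knew the block length or held the list; an independent list holder may be described in material not shown. A waiting list implies booking ahead, which Step 3 shows removes most of the certainty. Both stems are in the same short-stem class and share eligibility criteria and broach-only preparation, so the article gives no evident motive for steering patients. All of this stands and limits the size of the problem. It does not remove it: the envelope cannot prevent counting, and the article describes the scheme as the study team's own without placing the list elsewhere.

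A reader might infer more than the text supports:

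- **That 15 allocations were known at selection.** That is the ceiling at L = 0.
- **That the claimed stratification is impossible.** Blocks of consecutive procedures do read like one chronological series, and no factor is named. Separate envelope series per stratum are not excluded, however, and the factors may be in the full protocol.
- **That baseline tables could not show such selection.** Patient selection lists a standard preoperative radiological assessment, from which bone stock and femoral shape might be read.
- **That publishing the block length exposed the allocations.** The randomisation section is in the past tense, and publication cannot help predict allocations already made.

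**Conclusion.** The concern holds in limited form. One stated block length, with a single operator who supplies the patients and knows past allocations, leaves some late-block allocations open to inference despite the envelopes. Under the assumptions in the working, certainty ranges from at most about 15 of 90 down to near zero with three or more patients booked ahead; correct guessing ranges from 65% down to 53% with five booked ahead. The documents do not show that any allocation was predicted or acted on, or that the surgeon knew the block length. This supports an inexpensive improvement, not a conclusion that the randomisation failed.

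**What to change.** For any patients still to be randomised:

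1. Generate a new list with randomly varying block sizes, not disclosed to the operating and screening team. Do not simply substitute a shorter fixed block.
2. Have existing staff outside that team prepare and hold the list.
3. Record the eligibility decision, including the judgement on bone stock and deformity, before the operating date is assigned.

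For patients already randomised, report the fixed block length with a single operator as a limitation. The article mixes past tense for randomisation with future tense for recruitment and surgery, so the sponsor should first establish whether any envelopes remain. If none do, only the limitation statement applies.

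The cost is a new list and envelopes, a short amendment, and a possible final imbalance of a few patients between arms.

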#### Intervention

All patients will receive the type of implant to which they have been randomly allocated and thus two groups of patients will be created: group A: Tri-Lock BPS group and group B: Minima S Monolithic Femoral Stem implantation group.

The same senior surgeon (PM) will perform all the arthroplasties with a standardized operative technique through a mini-posterior approach. The femur will be prepared in a broach-only fashion and then the prosthesis will be impacted until a tight metaphyseal fit is achieved. The acetabulum will be prepared in a standardized fashion according to the manufacturer’s manual with the intention of using larger femoral heads (28–32 mm). Ceramic or polyethylene inserts and ceramic or metallic heads in respect will be used according to surgeon’s preference and patients age. All patients in both groups will undergo the same postoperative physiotherapy protocol, which consists of gradual progression from up-to-chair tolerance to ambulation and stair-climbing under the supervision of a certified physical therapist. Patients who manage to complete inpatient physical therapy for independent full weight-bearing would be discharged from further therapy but those with less compliance will continue further rehabilitation.

#### Radiographic evaluation

All antero-posterior pelvis radiographs will be obtained in a similar manner with both legs internally rotated 15^0^, and with bony landmarks (teardrop and lesser trochanter) clearly visible. All radiographic measurements will be performed with AutocadTM software. To test the reliability of the measurements, two independent examiners will review all radiographs. Intra- and inter-rater reliability will be assessed using intra-class correlation coefficients (ICC). Radiographs will be calibrated, and corrected for any magnification based on the known size of the femoral head. Femoral prosthesis fitting, alignment and stability will be assessed. Varus, valgus or neutral implant position will be checked at the first postoperative radiograph by measuring the angulation along the stem relative to the femoral shaft. Stem alignment is considered normal if its deviation from the axis of the femoral shaft is 5^0^ or less. Varus or valgus inclination of the stem relative to the canal of over 5° is defined to be malpositioned [50–52]. In both groups, all follow-up radiographs will be examined for signs of bony ingrowth or signs of loosening and will be classified as osseointegrated, fibrous stable or unstable [53]. To assess stability, length measurements from the superior tip of the greater trochanter to the lateral border of the implant between immediate postoperative and subsequent follow-up visits will be compared. A progressive axial subsidence of > 3 mm, a varus or valgus shift of > 3^0^ and the detection of a complete radiolucent line surrounding the entire porous-coated surface on both the antero-posterior and the lateral radiographs will be considered signs of possible loosening that needs further investigation [50–52, 54–56] such as bone scan. Osteolysis is defined as any discretely localized radiolucency adjacent to the femoral implant, if it is detected on follow-up radiographs but was absent in the immediate postoperative radiographs. The sites of any osteolytic lesions around the femoral component will be recorded according to the classification of Gruen et al. [57]. Given the lack of distal stem in the short femoral components, region from the lower border of the lesser trochanter to the tip of the greater trochanter was defined as zone 1, and the region from the lower border of the lesser trochanter to the femoral neck cut level was defined as zone 7 according to Kim et al. [50]. Pedestal formation will be diagnosed in the presence of bone formation bridging partially or completely the intramedullary canal [6]. Hypertrophies, atrophies, seam formations and spot welds, sclerotic lines in the form of a neocortex as well as periarticular ossifications according to Brooker [58] will be also recorded.

#### Outcome assessment (Fig. 5)

Patient-reported outcome measures

All eligible patients will complete the Greek version of WOMAC [44] and the Greek version of SF-36 [45] questionnaires as well as the HHS [46] and the Numeric Pain Rating Scale (NPRS).b.Gait analysis

Supplementary to patient-reported outcome measures, functional assessment will be further investigated by gait analysis, using an inertial measurement unit (IMU: Free4Act [59, 60], Lor An Engineering, Bologna, Italy).

Motion analysis is based on three different physical performance tests: (1) gait along a 12-m walkway at the patient’s self-selected normal speed, (2) 12-m gait at high speed in respect to patient’s functional status and (3) the Up and Go Test. The sensor is composed of a three-axis accelerometer (max range ± 6 g), a three-axis gyroscope (full scale ± 300°/s) and a three-axis magnetometer (full scale ± 6 gauss). The Free4Act sensor is positioned at the dorsal side of the pelvis, centrally between both posterior superior iliac spines. Spatiotemporal gait parameters will be recorded, including: walking speed (m/s), cadence (steps/min) and affected leg step time (s), step length (m), step time irregularity (%), stance and swing phase duration (% of gait cycle). The range of motion (ROM; degrees) of the pelvis in frontal plane (i.e., pelvic obliquity) will be further calculated through the inertial sensor’s inbuilt integration of the gyroscope signals.c.Reporting of complications/patient satisfaction

All intra-operative and post-operative complications will be recorded. At every outpatient visit, patients will be also asked for the presence or absence of thigh pain. If the answer is “yes,” patients will be further asked whether the pain is at rest or during activity and how often they have thigh pain (all the time, most of the time, some of the time, a little of the time, or never). At the 1-year appointment and yearly thereafter, patient satisfaction [47, 48] with the outcome will be assessed and categorized as: overall satisfaction, satisfaction with pain relief, functional improvement to perform daily activities and satisfaction with ability to perform recreational activities. Patients will be classified as very satisfied, somewhat satisfied, somewhat dissatisfied and dissatisfied.

#### Follow-up assessments

Clinical and radiographic follow-up assessments are scheduled at 3, 6 and 12 months and annually thereafter for a minimum of 2 years’ follow-up. Each visit will include clinical and radiological examination with antero-posterior and frog-leg lateral views of the pelvis. All patients would again fill up the HHS, WOMAC, SF-36 and NPRS scale. At the 1-year appointment and yearly thereafter, patient satisfaction with the results of THA will be assessed and gait analysis will be also performed (Fig. 5).

#### Analysis

##### Power and sample size calculation

The minimal clinically important differences (MCID) for sample calculation have been defined according to the literature at 25 points for the WOMAC score, 20 points for the HHS and 12% difference for the SF-36 score. In order to achieve a 80% power or better the effect size is expected to lie between 0.25 and 0.6, suggesting a sample size of 45 patients in each group [61].

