### Clinical study

#### Study aims

The main purpose of this study is to compare the functional and radiological results of short-stem THA using the TRI-LOCK BPS and the Minima S Femoral Stem, measured by validated clinical scores including gait analysis and standardized radiological parameters up to a minimum of 2 years’ follow-up.

The primary endpoint will be (1) the incidence of all hip-related complications up to 2 years after surgery and (2) change in health-related quality of life assessed with Western Ontario and McMaster Universities Osteoarthritis Index (WOMAC [44]) and the 36-item Health Survey (SF-36) [45] scores up to 2 years. Hip-related complications are defined as intra- and postoperative fractures, dislocation, wound infection, early or late loosening and revision surgery of any implant for any reason. The secondary endpoints at 1- and 2-years’ outcomes include hip function evaluated with the Harris Hip Score (HHS) [46], the Numeric Pain Rating Scale (NPRS), patient satisfaction [47, 48] and the parameters of gait analysis ((a) gait along a 12-m walkway at the patient’s self-selected normal speed, (b) 12-m gait at high speed in respect to patient’s functional status and (c) the Up and Go Test).

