##### Statistical analysis

Analysis will be by intention to treat. Differences between groups will be estimated using either the *t* test or Wilcoxon test at the 5% significance level to compare the distribution of the primary endpoint between the treatment samples. The patient outcome scores will be assessed with repeated measures analysis of variance (ANOVA) models to account for the repeated data collection time points. Results will be presented as an adjusted mean difference with its corresponding 95% confidence intervals.

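### The WOMAC and HHS MCIDs presented as the basis of the sample size do not fit the stated effect sizes of 0.25 to 0.6, and 45 per group delivers 80% power only at about 0.6

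*Protocol article*

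**What the plan says.** The *Power and sample size calculation* section of the protocol article (Clinical study, Analysis) makes two consecutive statements.

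- It sets thresholds and ties them to the sample size: the MCIDs behind the calculation were "defined according to the literature at 25 points for the WOMAC score, 20 points for the HHS and 12% difference for the SF-36 score".
- It then gives the result. For a power of at least 80% it says that "the effect size is expected to lie between 0.25 and 0.6", and from this it draws the recruitment target, "suggesting a sample size of 45 patients in each group".

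The section does not say what kind of effect size is meant, and no step turns the MCIDs into it. The clinical *Statistical analysis* section tests the primary endpoint "using either the *t* test or Wilcoxon test at the 5% significance level", uses repeated measures ANOVA for the outcome scores, and promises adjusted mean differences with 95% confidence intervals. The clinical *Study aims* section makes "change in health-related quality of life assessed with Western Ontario and McMaster Universities Osteoarthritis Index" and SF-36 part of the primary endpoint. HHS is secondary.

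**The concern.** A standardised effect size is a difference divided by a standard deviation. Giving both the difference and the effect size therefore fixes the SD, and the result can be checked against what the scale allows. For WOMAC and HHS it does not look credible.

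What is at stake is how the result will be read. A reader will believe that the trial was sized on a 25-point WOMAC difference and may take a significant result as evidence of a difference of that order. If 45 per group in fact targets about 0.6 SD, significance can arise from a WOMAC difference far below the trial's own threshold of importance.

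**Working it through.** **Inputs from the article:** MCIDs of 25 (WOMAC), 20 (HHS) and 12% (SF-36); effect size 0.25 to 0.6; power 80%; 5% level; 45 per group.

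**Assumptions:** two-sided test; effect size is the standardised mean difference d; all 45 per group are analysed; WOMAC and HHS scored 0-100; 12% read as 12 points; SD of the analysed outcome 15 to 25 points where a range is needed. The article gives neither the score ranges nor the SDs.

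**1. Reproducing the 45.** n per group = 2(1.96 + 0.84)² / d².

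- d = 0.6: 15.70 / 0.36 = 43.6, so 44 (45 with the t distribution). The stated figure is reproduced.
- d = 0.25: 15.70 / 0.0625 = 251.2, so 252 (253 with the t distribution).
- Power with 45 per group: 80% at 0.6 and about 22% at 0.25 (32% if one-sided).

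The 45 belongs to the upper end of the range only.

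**2. Implied SD = MCID / d.**

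| Score | MCID | SD at d = 0.6 | SD at d = 0.25 |
|---|---|---|---|
| WOMAC | 25 | 41.7 | 100 |
| HHS | 20 | 33.3 | 80 |
| SF-36 | 12 | 20 | 48 |

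**3. What the scales allow.**

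- *Score at one visit, 0-100.* The SD cannot exceed 50. If the two arm means differ by the MCID, the largest common SD is √(37.5 × 62.5) = 48.4 for WOMAC and √(40 × 60) = 49.0 for HHS. SDs of 100 and 80 are impossible. At d = 0.6 the implied SDs are 41.7/48.4 = 86% and 33.3/49.0 = 68% of the ceiling, and both exceed the SD of a uniform spread over the scale (100/√12 = 28.9).
- *Change score, -100 to +100.* The ceiling is √(87.5 × 112.5) = 99.2 for WOMAC and √(90 × 110) = 99.5 for HHS. WOMAC at 100 is still ruled out. HHS at 80 is possible only in theory. At d = 0.6, SDs of 41.7 and 33.3 are within bounds; about 95% of a roughly normal distribution would then lie within 1.96 SD, or 82 and 65 points, either side of the mean change.

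**4. SF-36.** With 12 points and an SD of 20, d = 0.6 and n = 45 by t test. It is the only one of the three MCIDs that gives the 45 at an SD within 15 to 25.

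**5. What the MCIDs would need, and what 45 detects.** The smallest d with 80% power at 45 per group is 0.597.

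| SD (assumed) | d for 25 WOMAC points | n per group (t test) | Difference detectable with 45 | Share of 25 |
|---|---|---|---|---|
| 15 | 1.67 | 7 | 9.0 | 36% |
| 20 | 1.25 | 12 | 11.9 | 48% |
| 25 | 1.00 | 17 | 14.9 | 60% |

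For 20 HHS points at the same SDs, d is 1.33 to 0.80 and n is 10 to 26 per group.

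**6. Other readings.** For two equal groups Cohen's f equals d/2, so 0.25 to 0.6 would mean d = 0.5 to 1.2. The implied SDs become 20.8 to 50 (WOMAC) and 16.7 to 40 (HHS), and the ends of the range need 64 and 12 per group; 45 corresponds to f = 0.3. A one-sided test needs about 199 and 36 per group at d = 0.25 and 0.6. Averaging two to five repeated measures with correlations of 0 to 0.5 lowers n to 51-189 at d = 0.25 and 9-33 at d = 0.6, but leaves the implied SDs of step 2 unchanged. None of these brings the MCIDs, the whole range and 45 into agreement.

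**The case against.** **The 45 may come from SF-36.** With several scores, the most demanding one sets the sample size, and spare power for the others is no contradiction. This stands. A reader might infer that the 45 has nothing to do with any stated MCID; the article does not support that, because SF-36 is a primary score and can give d = 0.6 and 45. It does not explain the rest of the range, and the text presents WOMAC and HHS on the same footing as SF-36.

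**The primary endpoint is change, so a ceiling of 50 is the wrong bound.** This also stands. For change scores only the WOMAC SD of 100 is strictly excluded, and a uniform spread has SD 200/√12 = 57.7, so 33 and 42 are not beyond it. For the rest the word is implausible, which is a judgement; HHS at 33 is the mildest case. If WOMAC were summed on a wider scale such as 0-240, its SDs would be possible as well, leaving the HHS mismatch.

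**The metric is undefined and an article may leave the SD to the full protocol.** Agreed: a missing SD is not the point. The point is that two printed statements, one offered as the basis of the other, do not agree on any reading tried.

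**Any trial can reach significance below its MCID.** True, but the degree differs. A trial with 80% power at its MCID reaches significance from about 1.96/2.80 = 70% of it. Here the boundary is about 1.99 × √(2/45) = 0.42 SD, or 6.3 to 10.5 points at SDs of 15 to 25: 25% to 42% of the 25-point MCID.

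**Conclusion.** The concern holds as a wrongly stated basis for the sample size. The WOMAC and HHS MCIDs cannot credibly be the source of effect sizes of 0.25 to 0.6, and 45 per group supports only the top of that range. The trial is in effect sized for a difference of about 0.6 SD, roughly 9 to 15 WOMAC points if the SD is 15 to 25.

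A reader might also infer that 45 per group is too few for the stated WOMAC and HHS MCIDs. The reverse holds: at those SDs power for them is about 97% or more. The shortfall is for small effects, near the 0.25 that the same sentence cites.

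The conclusion rests on reading effect size as a standardised mean difference, on 0-100 scales and on the illustrative SDs. The power figures at 0.25 and 0.6 need neither the scales nor the SDs. It should be corrected, but it does not threaten the conduct of the trial.

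**What to change.** Revise the *Power and sample size calculation* section as follows.

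1. Replace the range 0.25 to 0.6 with the effect size that 45 per group detects: about 0.6 SD at 80% power, two-sided 5%.
2. Name the primary score that drove the 45, with its SD and source, and give the detectable difference in points (0.6 × SD; for example 12 points if the SD is 20). If it was SF-36, say whether 12% means 12 points.
3. Remove the statement that the WOMAC and HHS MCIDs defined the sample size, or show the calculation that links them.
4. Add to the clinical *Statistical analysis* section that the 95% confidence interval for the 24-month difference will be read against the MCID of that score, so that significance alone is not called clinically important.

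The cost is wording only. No patients, visits or analyses are added, since the confidence intervals are already planned.

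### The 80% power tied to effect sizes of 0.25 to 0.6 holds, for the planned two-group test, only at 0.60; with 45 patients per group it is about 22% at 0.25

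*Protocol article*

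**What the plan says.** In the protocol article, under Power and sample size calculation, a single power floor and a single sample size per group are attached to a range of effects: to "achieve a 80% power or better the effect size is expected to lie between 0.25 and 0.6, suggesting a sample size of 45 patients". Minimal clinically important differences are listed for WOMAC, HHS and SF-36. No standard deviation, effect-size scale or sidedness is given, and the text does not say at which point of the range the 45 was calculated.

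Under Statistical analysis of the clinical study, a t test or Wilcoxon test between groups is planned "at the 5% significance level to compare the distribution of the primary endpoint between the treatment samples". The same paragraph adds: "The patient outcome scores will be assessed with repeated measures analysis of variance (ANOVA) models". Results are to carry 95% confidence intervals.

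**The concern.** Required sample size grows with the inverse square of the effect size. From 0.6 down to 0.25 the effect shrinks by a factor of 2.4, so the number needed grows by about 2.4² = 5.76. One sample size therefore cannot just meet an 80% floor at the top of this range and also meet it at the bottom, unless it is far larger than the top requires.

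Change in WOMAC and SF-36 is part of the primary endpoint, and the Discussion expects that even subtle differences in stem geometry may affect clinical performance, so small differences are of interest. Someone relying on the power statement would expect the trial to detect an effect of 0.25 four times in five, and would give a non-significant result more weight than it can bear.

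**Working it through.** **Inputs.** From Power and sample size calculation: 45 per group, power of at least 80%, effect size 0.25 to 0.6. From Statistical analysis: two-group t test, 5% level. Assumed: a two-sided test (in line with the 95% intervals), equal variances, complete data, and effect size d = difference in means / SD.

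**Step 1: reproduce the plan's figure.** Normal approximation, n per group = 2(1.960 + 0.842)² / d².
- d = 0.6: 2 × 7.849 / 0.36 = 43.6, so 44.
- The exact t-test calculation gives 44.6, so **45**. The plan's number is reproduced at the top of its range.

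**Step 2: the same calculation lower in the range.**
- d = 0.5: exact 63.8, so 64 per group.
- d = 0.25: 2 × 7.849 / 0.0625 = 251.2, so 252; exact 252.1, so **253** per group.

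**Step 3: power with 45 per group.** Noncentral t with 88 degrees of freedom, noncentrality d√(45/2) = 4.743d, critical value 1.987.

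| d | Noncentrality | Power |
|---|---|---|
| 0.25 | 1.19 | 21.6% |
| 0.30 | 1.42 | 29.1% |
| 0.40 | 1.90 | 46.7% |
| 0.50 | 2.37 | 65.0% |
| 0.55 | 2.61 | 73.2% |
| 0.60 | 2.85 | 80.4% |

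Solving for d, power reaches 50% at 0.418 and 80% at **0.597**.

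**Step 4: other analyses with d = 0.25.** Power is 32% one-sided, 21% for the Wilcoxon test on normal data, 27% to 50% for analysis of covariance with an assumed baseline correlation of 0.5 to 0.8, and 24% to 42% for the mean of 2 to 5 visits with an assumed correlation of 0.3 to 0.8. None comes near 80%.

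**Step 5: 0.25 read as Cohen's f.** For two equal groups d = 2f = 0.5.
- Two-group test: noncentrality f²N = 0.0625 × 90 = 5.625, power 65.0%.
- Mean of m visits with between-visit correlation r: noncentrality f²Nm / (1 + (m − 1)r). With m = 4 this gives 9.00 and 84.3% at r = 0.5, 8.04 and 80.1% at r = 0.6, and 7.26 and 75.9% at r = 0.7.
- Group-by-time test: noncentrality f²Nm / (1 − r). Power is about 98% or more for 2 to 5 measurements with r of 0.3 to 0.8.

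The correlations and numbers of measurements in this step are assumptions; the article gives no correlation.

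**Side check: margin at 0.60.** With 40 analysed per group, power at d = 0.6 is 75.5%.

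**The case against.** The strongest reply is that the sentence is ambiguous rather than false. It names no scale, it cites a source for the calculation, and the article plans repeated measures ANOVA for the scores, where 0.25 is a plausible Cohen's f. Under that reading the average of four visits exceeds 80% power with correlations up to about 0.6, and a group-by-time test exceeds it comfortably. This stands as a possibility, and it would be wrong to say that no reading can rescue 0.25. It does not remove the point: the article states neither that scale nor a correlation, and 45 is exactly the t-test answer at d = 0.6. The sentence might also mean only that 80% power requires an effect somewhere in the range. That too fails for the two-group test below about 0.60.

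Three stronger readings are tempting and should be resisted.
- A reader might infer that any difference in the stated range would usually be missed. Power passes 50% at about 0.42, so this is untrue for roughly the upper half of the range.
- A reader might infer that the trial will declare the stems equivalent after a null result. The article plans no equivalence or non-inferiority conclusion; its hypothesis is of a difference.
- A reader might infer that the calculation assumed no losses. The article is silent on retention, and under Patient selection it invites withdrawing patients to give final primary endpoint data. The figure for 40 per group therefore shows only that there is no spare margin at 0.60.

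**Conclusion.** The point holds as a misstatement of power for the planned two-group comparison. With 45 per group, 80% power is available for standardised differences of about 0.60 and above, and falls to 65% at 0.5, 47% at 0.4 and 22% at 0.25. This rests on reading the effect size as a standardised mean difference, a two-sided 5% test and complete data. The first is the natural reading, because it alone reproduces 45 from the stated inputs without further assumptions. If Cohen's f in a repeated measures model was intended, the power claim may be defensible, but the sentence is then incomplete in the inputs on which it depends. In both cases it needs to change. The sample size itself is not shown to be wrong; what is wrong is the range of effects it is said to cover.

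**What to change.** Replace the power sentence with wording such as:

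> *45 patients per group give 80% power (two-sided 5%, two-sample t test, complete data) for a standardised between-group difference of 0.60 in a primary outcome score (WOMAC or SF-36 change); power is 65% at 0.5, 47% at 0.4 and 22% at 0.25.*

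No longer present 0.25 as an effect for which the trial is powered. Add that a non-significant result does not exclude differences below about 0.6 SD. The wording deliberately names no single primary score or visit, because Study aims defines the primary endpoint through both scores up to 2 years.

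If Cohen's f in a repeated measures ANOVA was meant, state instead that scale, which test is powered (between groups or group by time), the number of measurements and the assumed correlation.

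The cost is wording only: no more patients and no change to the analysis. The downside is that the stated power becomes less favourable.
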